EMA involves frequent surveys about behaviors and experiences in real time, often via SMS text messaging or mobile apps [24-26], making it a particularly appealing methodology for native smartphone users such as AYAs. EMA offers several distinct advantages for advancing adherence science by reducing recall bias, increasing real-world generalizability, and providing multilevel data on how adherence behaviors play out over time, place, and context [27]. In a pilot study, we demonstrated that implementing daily EMA for 6-MP adherence, across 28 days, was feasible and acceptable for AYAs with leukemia [28]. AYAs were more likely to miss a dose of 6-MP on weekends and on days when their adherence motivation and negative affect were worse relative to their typical functioning. Although these findings were novel and offered potential decision rules to test in future trials (eg, *deliver a medication reminder on weekends when AYA may be more prone to forget*), they require replication with a larger sample, over a longer period of time, and including AYA’s caregivers who are often intricately involved in cancer medication management (in one study, 73% of caregivers were responsible for managing these medications) [17].

A challenge with EMA and mHealth tools, in general, is rapidly declining user engagement [29-32]. All the methodological advantages of EMA are weakened if participants miss substantial surveys or stop responding altogether [29]. Moreover, AYAs with the greatest treatment adherence challenges—who would stand to benefit the most from an adherence-promotion intervention—may be the least likely to engage with EMA [28,33]. Although our pilot study demonstrated relatively high and stable EMA survey completion rates (mean 88.9%, SD 16.7%), there was substantial variability (range 39.3%-100%), and users were compensated US $2 for completing all 14 survey questions per day (up to US $56 total across 28 days) [28]. Financial incentives are an effective method to promote mHealth engagement in the short term; however, evidence supporting their long-term efficacy is mixed, and they may not be scalable in real-world clinical settings [34].

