### Objectives

In this study, we adopted and refined an open-source EMA app called SARA [38] for an AYA cancer population (renamed ADAPTS [Adherence Assessments and Personalized Timely Support]). Through using this app, our primary study aim is to determine the temporal associations between daily contextual factors and 6-MP adherence. We draw on the pediatric self-management model [39], a social-ecological theoretical framework of disease self-management and treatment adherence, focusing primarily on the individual-and family-level contexts that could affect day-to-day medication adherence. Specifically, we hypothesize that daily fluctuations in intrapersonal (eg, physical symptoms, negative mood, and low motivation) and interpersonal or environmental (eg, a dyadic AYA-caregiver disagreement and being outside of the home without caregivers) factors will increase the odds of missing 6-MP that day. In a secondary exploratory aim, we will explore the proximal impacts of theory-informed engagement strategies (reciprocity and nonmonetary reinforcements) on daily EMA survey completion. Our approach is consistent with the first step of the Behavior Change Theories, User-Centered Design, and Social Marketing framework, a comprehensive model for creating mHealth tools, which recommends conducting a situational analysis of the contextual factors associated with a health problem [40], as well as the preparation phase of the multiphase optimization strategy [41] comprised of gathering initial information to decide which set of (engagement) components to include before an optimization trial. These formative data will ultimately inform the creation of the first JITAI for improving AYA oral chemotherapy adherence while running a concurrent JITAI for promoting EMA engagement. Improving the precision of adherence-promotion interventions in this manner may significantly benefit AYAs who require frequent self-administration of medications, as static interventions have yielded small and heterogeneous effects [42,43].

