### Primary Data Analyses

This data set will consist of 30 AYA-caregiver dyads×63 days=a maximum of 1890 daily observations. EMA predictors include data from AYAs, caregivers, or dyadic data from both reports (eg, agreement between AYAs and caregivers that they had a disagreement that day). Tables and graphs will be created to demonstrate how 6-MP adherence varies by individual (physical symptoms, mood, and motivation), family (family disagreements and problems with communication), and social-environmental factors (time of day, day of the week, month of the year, where AYAs were, and who they were with). Mixed effects models will be used through SAS PROC GLIMMIX (SAS Institute) to examine whether EMA of contextual factors predicted the binary daily 6-MP adherence outcome. Separate mixed effects models will be constructed for different predictors and include the predictor as the fixed effect and a random intercept for each participant to account for between-person variability. Mixed effects models may also include demographic and treatment covariates (eg, race, ethnicity, and time since cancer diagnosis) as fixed effects if they demonstrated a significant association with the outcome. We will decompose the between-subject and within-subject effects of EMA of contextual factors by creating two predictors from the original score: (1) the individual mean across all time points (between-subject predictor) and (2) the deviation of the daily score from the individual mean (within-subject predictor). Given the embedded engagement strategies, we expect minimal missing data, and mixed effects modeling will be able to use all available outcome data and provide valid inferences if missingness is at random. However, we will examine the amount and pattern of missing data, and if missing is suspected to be not at random, sensitivity analyses will be performed to assess the robustness of the primary analysis results. Significant findings will inform tailoring variables for future JITAIs (eg, tailor messages based on affect, motivation, and day of week).

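### The daily context models carry no weekend term, so a context that merely differs at weekends could appear to be a same-day risk factor for missed 6-MP

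*Protocol article*

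**What the plan says.** All references are to the protocol article.

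- **Model form (Primary Data Analyses).** "Separate mixed effects models will be constructed for different predictors". These models "include the predictor as the fixed effect and a random intercept for each participant".
- **Adjustment (same section).** The models "may also include demographic and treatment covariates (eg, race, ethnicity, and time since cancer diagnosis"), each entered only if significantly associated with the outcome.
- **The tested coefficient (same section).** Each context is split into the person's mean over all days and "the deviation of the daily score from the individual mean (within-subject predictor"). The second part carries the Objectives hypothesis that a day's context raises the odds of a missed dose on that day. Among the contexts hypothesised there is "being outside of the home without caregivers".
- **Weekend as a correlate of the outcome (Background).** In the sponsor's pilot, "AYAs were more likely to miss a dose of 6-MP on weekends". The article says of the pilot findings that "they require replication with a larger sample".
- **Where day of week does appear (Primary Data Analyses).** Tables and graphs will show adherence by "social-environmental factors (time of day, day of the week, month of the year, where AYAs were, and who they were with"). Day of week is also an example of a tailoring variable that significant findings could inform. Nothing places it in the model of another context.

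**The concern.** The random intercept and the person-mean centring remove stable differences between participants. They do not touch anything that varies from day to day within a participant, and weekend does. If doses are missed more often at weekends and a context is also more common or more intense then, the within-person coefficient of that context absorbs part of the weekend effect.

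The covariates named as examples cannot help. Race and ethnicity are constant within a person. Time since diagnosis, if it is updated at all, drifts slowly and does not separate a Saturday from a Tuesday.

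Location and company are the contexts most plausibly tied to the weekend: the survey's answer options include school, classmates and friends.

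The stake is the use made of a significant result. Significant findings are to inform tailoring variables, and the Discussion says the results will help decide which survey questions are retained. Day of week is known without asking anyone. An item that only marks Saturday and Sunday would add survey burden and no information, and the same-day hypothesis would appear supported when it is not.

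**Working it through.** The plan gives no figure on this point to reproduce. Its row count is consistent: 28 + 35 = 63 days, and 30 × 63 = 1890 rows at most.

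**Inputs from the article.** 30 AYAs, 63 days each, 20% missed doses, two-sided 5% level, within-subject correlation 0.5. Weekend days per AYA: 63 × 2/7 = 18.

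**Assumptions.** The article gives only the direction of the weekend association. Assumed weekend odds ratios for a miss are 1.5, 2 and 3, with 1 as a control. The weekend shifts in context are also assumed. The true odds ratio of the context is 1 throughout.

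**Step 1: size of the spurious association, by hand.** Take a weekend odds ratio of 2 and ignore differences between persons. A 20% overall miss rate requires a weekday risk p0 and a weekend risk p1 with (5/7)p0 + (2/7)p1 = 0.20 and odds(p1) = 2 × odds(p0). This gives p0 = 0.166 and p1 = 0.285.

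For a context present on 30% of weekend days and 15% of weekdays:

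- Share of exposed days that fall at a weekend: (2/7 × 0.30) / (2/7 × 0.30 + 5/7 × 0.15) = 0.444.
- Share of unexposed days that fall at a weekend: (2/7 × 0.70) / (2/7 × 0.70 + 5/7 × 0.85) = 0.248.
- Miss risk when exposed: 0.166 + 0.119 × 0.444 = 0.219. When unexposed: 0.166 + 0.119 × 0.248 = 0.196.
- Apparent odds ratio: (0.219/0.781) / (0.196/0.804) ≈ 1.15.

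For 40% vs 10%, the weekend shares are 0.615 and 0.211, the risks 0.239 and 0.191, and the apparent odds ratio about 1.33. Simulation with person intercepts gave 1.15 and 1.34.

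**Step 2: how often this reaches significance (simulation).** Binary contexts, weekend odds ratio 2, person SD 1.3 on the logit scale, 1,000 simulated studies per setting:

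| Weekend vs weekday exposure | False positives without weekend term |
|---|---|
| 30% vs 15% | 14% |
| 40% vs 10% | 44% |

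Continuous contexts, conditional score test, 3,000 studies per setting; ranges are over person SD 1.0 and 1.81 (the latter a latent correlation of 0.5):

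| Weekend shift | Weekend OR 1.5 | OR 2 | OR 3 |
|---|---|---|---|
| 0.25 SD | about 6% | about 9% | 13–17% |
| 0.5 SD | 9–11% | 19–22% | 40–50% |
| 1 SD | 21–24% | 50–58% | 87–94% |

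**Step 3: controls and the adjusted analysis.** With a weekend odds ratio of 1, or with no weekend shift, the unadjusted rate stays near 5% (4.3% to 5.6%). Stratifying by weekend gives 4.2% to 5.8% in every setting.

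A random-intercept logistic model with person mean and daily deviation, close to the planned form, was run 250 times per setting at weekend odds ratio 2 and SD 1.81. It gave 20% (0.5 SD) and 51% (1 SD) without the weekend term, against 4.4% and 3.6% with it. The mean spurious odds ratio in that check was only about 1.08 to 1.14 per SD.

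**Step 4: incomplete surveys.** The runs above use all 1890 rows. At the 62.3% completion reported for the parent app, with random missingness, a re-run of the two binary cases fell from 14.7% to 10.7% and from 43.6% to 29.6%. At the pilot's 88.9% completion the rates barely changed.

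**The case against.** **The article is condensed.** A list of time-varying adjusters is often left to a statistical analysis plan, the covariate wording is permissive and its examples are open. This stands in part: a reader might infer that the plan rules out weekend adjustment, and the text does not go that far. But the article does more than stay silent. It states the content of each model and the class of covariates that may join it, and weekend is neither demographic nor treatment.

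**Day of week will be examined.** So it will, descriptively and possibly in a model of its own. A separate model adjusts nothing in the others.

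**The aim is association, and a marker of high-risk days is useful.** A context that tracks weekends does have a real marginal association with missed doses. But the hypothesis is worded as contexts increasing the odds of a miss, and an item that duplicates the calendar has no incremental value for tailoring. It is fair to add that significance alone will not fix the later intervention: the Future Directions section brings in a research team, theory and other evidence.

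**Weekend might be taken for an established cause.** The documents do not support that. They report one pilot association awaiting replication.

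**Position in the clinic cycle might seem to confound in the same way.** Month 1 covers the whole cycle, and later bursts sit near mid-cycle, where the article says adherence may be lower. But nothing shows that any context varies with the cycle, and the effect was not quantified. It does not carry the point.

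**Conclusion.** The point holds as a weakness in a stated analysis. The within-person coefficient that tests the same-day hypothesis is left unadjusted for weekend, a day-level factor that the sponsor's own pilot associated with the outcome.

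The mechanism is certain if two conditions both hold: doses are missed more often at weekends, and the context differs at weekends. The size is not known, because the article gives neither quantity. At an assumed weekend odds ratio of 2, the false-positive rate runs from about 9% for a small shift (0.25 SD) to about 20% for 0.5 SD, and from about 14% to 44% for the two binary contexts. A weaker weekend effect or fewer completed surveys lowers these figures; if either condition fails, the rate stays at about 5%. The spurious odds ratios are modest, so the harm lies in choosing variables by significance rather than in a large misleading effect.

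Adjustment does not over-correct. A day's mood or company cannot change the calendar, so weekend lies upstream of the context, and the context's own effect is left intact.

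**What to change.** In Primary Data Analyses, add a sentence to this effect: every daily context model includes a weekend indicator as a fixed effect, irrespective of its significance; the within-person hypothesis is tested on the adjusted coefficient; and the unadjusted estimate is reported alongside. The two estimates together show whether an item says anything beyond the calendar.

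Days since the last clinic visit may be added as a sensitivity analysis.

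The cost is one degree of freedom per model and a slight loss of precision, with no new data, since the calendar date of each observation is already recorded. Full day-of-week coding would use 6 degrees of freedom and is not needed for this purpose.

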### Human Support and Monitoring

In addition to automated engagement strategies integrated within the app, there are a few prompts that are manually sent by a member of our study team. First, after completing the first week of EMA, a standardized SMS text message will be sent to each AYA or caregiver participant to inquire about app glitches and provide a reminder to use the electronic pill bottle. Second, when a participant does not answer surveys for 3 consecutive days, they will receive an additional standardized SMS text message offering in-the-moment support for any app glitches for a maximum of one time during each EMA burst. Third, each month, a research assistant will meet briefly with families during monthly clinic visits to remind them of the study, ensure that the family is refilling MEMS bottles with 6-MP, confirm that AYAs and caregivers still have access to ADAPTS, provide financial compensation for their participation in the prior month, and download adherence data from the prior month as well as share with the AYA’s primary oncology provider. This level of human support is similar to our other prior mHealth trials [31], including the SARA trial.

To monitor for technical glitches, study staff will pull survey and engagement data each day to review whether (1) participants completed the survey from the prior day, (2) the money earned corresponds with the intended payment schedule, (3) the push notifications were sent and at the right times, and (4) participants are using the most up-to-date version of the app. Study staff will also review the list of active study participants and manually turn surveys *on* and *off* depending on their EMA burst cycle. Any technical issues will be documented in a log and shared with a technology support team within 24 hours.

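### The within-person models name no adjustment for weekend or burst; the only covariates named are person-level ones, which cannot adjust a daily deviation

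*Protocol article*

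**What the plan says.** Under Primary Data Analyses the article sets out the content of the model. "Separate mixed effects models will be constructed for different predictors", and each will "include the predictor as the fixed effect and a random intercept for each participant to account for between-person variability". The score is split into two terms: "the individual mean across all time points (between-subject predictor") and "the deviation of the daily score from the individual mean (within-subject predictor").

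The only other terms named are optional. "Mixed effects models may also include demographic and treatment covariates (eg, race, ethnicity, and time since cancer diagnosis"), and they enter "as fixed effects if they demonstrated a significant association with the outcome". No significance threshold is given.

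Day of the week and month of the year are listed among the factors to be tabulated and graphed, and day of week returns as an example of a tailoring variable. Neither is named as an adjustment term in the models for other predictors. Burst, or month of study, is not mentioned in the analysis at all.

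Two other sections bear on this. Background reports from the pilot that "AYAs were more likely to miss a dose of 6-MP on weekends and on days when their adherence motivation and negative affect were worse" than usual for that person. Study Design samples every day of month 1, but in months 2-6 only one week around the midpoint between clinic visits, a time chosen because adherence may then be lower.

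**The concern.** The hypothesis under Objectives is within-person: daily fluctuations in context raise the odds of missing 6-MP that day. A confounder of that association must itself vary from day to day within a person. Race and ethnicity do not. The named adjustment therefore serves the between-subject term and leaves the daily term as it was.

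The variables that could confound the daily term are those that move with the calendar. The protocol's own pilot ties weekends to missed doses. Location and company plausibly change at weekends too, and mood may. Burst is a second candidate, because the protocol itself expects adherence to differ at the part of the clinic cycle that bursts 2-6 sample. With a separate model per predictor, neither is held constant when mood, symptoms, location or company is tested.

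The article says that significant findings will inform the tailoring variables. An item that only stands in for Saturday could be kept on that basis. It would add survey burden and tell a later intervention nothing that the calendar does not.

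**Working it through.** **1. Inputs from the documents.** 28 days in month 1 plus 5 × 7 = 35 later days gives 63 days. 30 × 63 = 1890 person-days, which matches the article. Two-sided alpha is 0.05, the rate of missed doses is 20% and the within-subject correlation is 0.5 (Sample Size and Power). The documents give no weekend effect, no weekend shift in any predictor and no drift. All such values below are assumptions, shown as a range.

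**2. Why a fixed trait cannot adjust the daily term.** Let d_ij = x_ij − mean_i(x). Within each person Σ_j d_ij = 0, so for any covariate c_i that is constant within person, Σ_i c_i Σ_j d_ij = 0. The two are orthogonal. In simulations of a random-intercept logistic model (30 people × 63 days, 200 runs per scenario), adding a person-level covariate related to both predictor and outcome moved the within-person log-odds ratio by at most 0.0042 in any run.

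**3. Weekend and a yes/no predictor, by hand.** Assume that weekend has OR 2.0 for a missed dose, that the chance of being away from home is 50% at weekends and 20% on weekdays, and that being away has no effect.
- Share of days away: 2/7 × 0.5 + 5/7 × 0.2 = 0.286.
- Weekend share of away days: (2/7 × 0.5)/0.286 = 0.50. Weekend share of home days: (2/7 × 0.5)/0.714 = 0.20.
- Missed-dose rates that average 20% with OR 2.0: 16.6% on weekdays, 28.5% at weekends.
- Missed when away: 0.5 × 16.6% + 0.5 × 28.5% = 22.5%. Missed when at home: 0.8 × 16.6% + 0.2 × 28.5% = 19.0%.
- Spurious OR: (0.225/0.775)/(0.190/0.810) = 1.24.

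A simulation of 600 trials with the actual burst structure gave OR 1.245, significant in 32% of trials. With weekend in the model it gave 1.00 and 5.5%.

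**4. The low end of the same calculation.** These cases pool 1890 days as if independent. That overstates rejection somewhat: for the case in step 3 it gives 42%, against 32% in the simulation.

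| Weekend OR | Away, weekend vs weekday | Spurious OR | Rejection |
|---|---|---|---|
| 1.5 | 30% vs 20% | 1.05 | 6.5% |
| 2.0 | 30% vs 20% | 1.09 | 10% |
| 1.5 | 50% vs 20% | 1.13 | 17% |

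**5. A continuous predictor.** These are the random-intercept simulations of step 2, with true within-person OR 1 and the shift in within-person SD. The person SD of 1.8 corresponds to a correlation of 3.24/(3.24 + 3.29) = 0.50 on the logit scale. Simulated missed-dose rates were 25% to 30%, somewhat above the protocol's 20%.

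| Weekend OR / shift | Study-month OR / shift | No time terms: OR, type I error | With weekend and month: OR, type I error |
|---|---|---|---|
| 1.5 / 0.2 | none | 1.018, 4% | 1.000, 3% |
| 2 / 0.3 | none | 1.052, 14% | 1.009, 7% |
| 2 / 0.5 | none | 1.079, 24% | 1.006, 5.5% |
| 3 / 0.5 | none | 1.115, 42.5% | 0.996, 2% |
| 2 / 0.3 | 2 / 0.5 | 1.096, 31% | 1.006, 4.5% |
| 2 / 0.5 | 2 / 0.5 | 1.118, 42% | 1.001, 7% |

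With 200 runs the standard error of a 5% rate is √(0.05 × 0.95/200) = 1.5 points, so the right-hand column is consistent with 5%.

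**6. Drift alone.** If the predictor and the log-odds of missing both drift by 0.3 per SD of burst number, the spurious OR is 1.10 (23% significant). With drifts of 0.3 and 0.5 it is 1.17 (61%). Adjusting for burst restores 1.00 and 5.5% to 6.5%.

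**The case against.** The covariates are optional and given by example, and time since diagnosis, if updated daily, would carry study time. The article does not say that it is updated, and it would enter only if significant. Day of week is among the factors examined, so calendar time is not overlooked. It is still not held constant when another predictor is tested.

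The stated objective is temporal association, and a marker of risky days can be useful whether or not it acts through weekends. That is fair, and it is a reason to report the unadjusted model as well. It does not dispose of the point, because the hypothesis is that daily fluctuations increase the odds of a missed dose.

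Some stronger readings are tempting, and the documents do not support them.
- A reader might infer that the person-level covariates are useless. They can serve the between-subject term, which the plan also estimates.
- A reader might infer that false tailoring variables will result. That depends on associations the documents do not report. With weak ones the bias is negligible, and all the spurious odds ratios above are far below the 2.8 per SD used for power.
- A reader might infer that adherence and context do drift across bursts, since staff "download adherence data from the prior month as well as share with the" oncology provider each month. Confounding would also need the predictor to drift in a common direction across people, and nothing in the documents shows this for any survey item.
- A reader might infer that centring on one overall mean is an error. Decomposition around the person mean is standard. Centring on the person-by-burst mean would change the estimand and leave a burst term almost nothing to do for the daily effect.

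**Conclusion.** The point holds as a moderate flaw in model specification that is cheap to mend. The adjustment named in the plan cannot reach the within-person effect, and weekend and burst, which the protocol's own text links to adherence, are absent from the models for the other predictors. Orthogonality is exact for the centred score and confirmed by simulation. The size is conditional: the spurious odds ratio ranges from about 1.02 with near-nominal error to about 1.25 with type I error near 32%, and it rests wholly on assumed weekend and drift effects. Type I error was higher still (up to 61%) in the strongest assumed scenarios. The main risk is choosing a tailoring variable that only reflects the calendar; the plan would not be creating a large effect from nothing.

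The significance screen is a lesser matter. With 30 participants it is a weak, data-driven way to choose between-subject covariates, but its effect was not quantified here.

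**What to change.** - Include weekend (yes/no) and burst (1 to 6, categorical) as fixed effects in every contextual-predictor model. Report the model without them alongside if marker value is of interest.
- Replace the significance screen with a short prespecified list of person-level covariates for the between-subject term, for example age and time since the start of maintenance.
- Treat centring on the person-by-burst mean as an optional sensitivity analysis at most.

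Cost: 1 degree of freedom for weekend and 5 for burst, so about 6, against up to 1890 person-days. Weekend and burst follow from the survey dates, so no new data, participants or procedures are needed.
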